## Methods: data collection, management, and analysis

5

### Type and classification of study- randomized control trial

5.1

*Intervention* – application of NIV by HELMET after randomizing the selected patients with odd and even numbers.

*Control group-* application of NIV with face mask after randomizing the selected patients with ARDS caused by COVID-19 and other pneumonia, type 1 and type 2 respiratory failure, Conscious and alert patients. NIV facemask will be applied as per the facial contour of the patient. NIV helmet is a transparent hood and size will be measured as per the head size. Both groups will have a standard protocol for titration if NIV. First, PEEP will be increased gradually to target spo2 above 90% with a Fio2 of 60% or less. Pressure support or IPAP will be increased slowly by 2 to 3 cm H2O to target a respiratory rate less than 30/min. The patient will be connected to non-invasive ventilation for 4 hours and will be on a high-flow nasal cannula for 1 hour. This 4:1 ratio will be continued till his condition improves or he will get intubated if he is worsening on non-invasive ventilation. Blood gases, oxygenation status [Po2/Fio2] will be monitored in both groups. The time of intubation will be the main comparison factor among the 2 groups. The intubation criteria will be the same for 2 groups which include, Worsening P/F ratio worsening acidosis, hemodynamic instability, poor neurological status.

The decision for intubation will be decided by the primary physician on duty

The intubated patient will be ventilated with lung-protective ventilation as per ARDS protocol.

If a patient in the control group is not tolerating the mask, they will be given the helmet in the other group as rescue therapy.

The weaning criteria will be the same for both groups and patients will be weaned to a high-flow nasal cannula or non-rebreathing mask. For weaning, pressure support and PEEP will be reduced gradually and will be discontinued if the respiratory rate is less than 30/min and P/F ratio more than 150 with a PEEP of 5 cm H20. If 1 patient is out of NIV for more than 12 hours a day for 48 hours, that will be considered as weaning.

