## Objectives

2

Primary objective: To assess the efficacy of non-invasive ventilation with HELMET in reducing endotracheal intubation rates in comparison with NIV face mask among patients with ARDS.

Secondary objective: to explore any improvement in oxygenation, time to intubation, ventilation days, and tolerance to HELMET NIV in comparison with facemask NIV.

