## Trial design

3

This is a phase-III, randomized, comparative, parallel assignment, open-label clinical study

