### Outcomes measures

4.4

Primary outcome measure:

1.Need for endotracheal intubation [ time frame: 6 weeks].Number of patients requiring endotracheal intubation after application of helmet device

Secondary outcome measures:

1.Improvement in oxygen saturation [time frame: 2 weeks]Improvement of oxygenation defined as “PaO2/FiO2 ≥ 200 or increase from baseline by 100”.2.Ventilator-free days [time frame: 28 days]Duration of mechanical ventilation via endotracheal tube.3.Intensive care unit length of stay [time frame: 4 weeks]The number of days admitted to the intensive care unit.4.Overall mortality [time frame: 90 days]Death from any cause during hospitalization at the time of enrollment.5.Need for proning [time frame: up to 24 weeks]Need for proning during the hospital stay.6.ICU mortality [time frame: 28 days]Death from any cause during ICU hospitalization at the time of enrollment.7.Patient tolerability [time frame: 28 days from randomization]The degree to which overt adverse effects of a drug can be tolerated by a patient, including feeding tolerance.

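### The primary event is an intubation decided by an unblinded duty physician on criteria without cut-offs, so the threshold may differ between arms

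*Protocol article*

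**What the plan says.** The primary objective (section 2) concerns "reducing endotracheal intubation rates in comparison with NIV face mask among patients with ARDS". Section 4.4 makes the primary outcome the need for intubation, counted over 6 weeks. Section 3 describes a "randomized, comparative, parallel assignment, open-label clinical study".

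Section 5.1 sets out how the event comes about:

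- Criteria: "The intubation criteria will be the same for 2 groups which include, Worsening P/F ratio worsening acidosis, hemodynamic instability, poor neurological status".
- Decision-maker: "The decision for intubation will be decided by the primary physician on duty".
- Visibility of the arm: "NIV helmet is a transparent hood and size will be measured as per the head size". The interface is therefore evident at the bedside.

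The same section gives numbers for other decisions. Titration has targets for SpO2 (above 90%), FiO2 (60% or less) and respiratory rate (below 30/min). Weaning has limits for respiratory rate (below 30/min), P/F ratio (above 150) and PEEP (5 cm H2O). Section 4.3 gives numbers for two exclusions (Glasgow Coma Scale below 13, pH below 7.15). The intubation criteria have none.

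**The concern.** The primary outcome is a clinical decision, and the person who takes it knows the arm. The interface cannot practicably be masked at the bedside, so reproducible criteria are the main protection against different handling of the two groups. The stated criteria are words of direction or degree. They carry no value, duration, reference measurement or number that must be met, and the wording leaves the list open. Two physicians could decide differently on identical findings and both comply. So could one physician with a helmet patient and a mask patient.

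The Introduction states the hypothesis that the helmet reduces intubation. Staff who share it might persist longer with a helmet patient; staff unfamiliar with the device might do the reverse. Either way, a threshold difference enters the primary comparison directly and looks the same as a treatment effect.

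**Working it through.** **Is there a plan figure to reproduce?** No. Section 4.6 gives a total of 60 with no alpha, power or assumed rates. The calculation below does not depend on how that number was reached.

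**Inputs**

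- Total 60 (section 4.6). Allocation by odd and even numbers is taken as 30 per arm: an assumption.
- Two-sided alpha 0.05: an assumption.
- Cited rates: 61.5% face mask, 18.2% helmet (Introduction, the one earlier randomized trial). These are the only intubation rates in the article.
- Average rate with no true effect: 40% is an assumption, varied from 30% to 61.5%.
- Threshold-only gap: an assumption. With 30 per arm, 10 points is 0.10 × 30 = 3 patients, and these must be patients whose event status at 6 weeks changes.

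**Method.** With a mask events and b helmet events out of n = 30 each, put p̄ = (a + b)/60 and

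z = [(a − b)/30] / √[p̄(1 − p̄) × 2/30].

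The result is significant if |z| > 1.96. The chance of a significant result favouring the helmet is the sum of Bin(a; 30, mask rate) × Bin(b; 30, helmet rate) over all significant pairs with a > b. The same sum was taken with Fisher's exact test.

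**(a) No true effect.** The gap is split evenly around the average. At 40%, a 10-point gap means 45% mask v 35% helmet.

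| Threshold-only gap | z-test, average 40% | Fisher, average 40% | z-test, averages 30% to 61.5% | Fisher, averages 30% to 61.5% |
|---|---|---|---|---|
| 0 | 2.4% | 1.3% | 2.4–2.6% | 1.3–1.4% |
| 5 points | 5.8% | 3.3% | 5.7–6.0% | 3.3–3.5% |
| 10 points | 11.9% | 7.5% | 11.9–12.9% | 7.5–8.3% |
| 20 points | 35.1% | 25.9% | 34.9–39.2% | 25.7–29.8% |

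A 10-point gap multiplies the false-positive chance in favour of the helmet by about five (11.9/2.4 = 5.0; Fisher 7.5/1.3 = 5.8). The choice of average rate hardly matters.

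**(b) True rates as in the cited trial, with the threshold working against the helmet.** Normal approximation:

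Power = Φ{ [d√n − 1.96√(2p̄(1 − p̄))] / √(p1(1 − p1) + p2(1 − p2)) }.

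- No gap: p1 = 0.615, p2 = 0.182, d = 0.433, p̄ = 0.3985. Power = Φ[(2.372 − 1.357)/0.621] = Φ(1.63) = 94.9%. Exact enumeration gives 94.6%.
- 10-point gap: p2 = 0.282, d = 0.333, p̄ = 0.4485. Power = Φ[(1.824 − 1.379)/0.663] = Φ(0.67) = 74.9%. Exact enumeration gives 75.7%.
- 20-point gap: 43.7%; exact 45.0%.

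**The case against.** The strongest reply has four parts.

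**Condensation.** A journal article shortens the full protocol, and numeric thresholds may stand there. This lowers certainty but does not remove the point. The article does print the criteria, claims they are the same, names the decision-maker, and gives numbers for titration, weaning and exclusion. The weakness lies in what it states.

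**Timing is not occurrence.** The outcome counts patients intubated over 6 weeks. Deferring or advancing an intubation changes that count only if the patient's final status changes. This stands, and the gaps above are defined that way. A reader might build an example such as 9/30 helmet v 15/30 mask from a common 12/30, with three decisions shifted in each arm, and call it a false finding. It treats every shift as a change of status, and the table is not significant (Fisher p = 0.19). It illustrates bias in the estimate only.

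**Records exist.** A reader might infer that nothing would show whether a criterion was met. Section 5.1 provides for blood gases and P/F to be monitored in both groups, and section 5.2 requires verifiable source documents. Values could be reviewed afterwards. What the article does not describe is a record of which criterion prompted the decision.

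**The high-flow hour.** A reader might also argue that a gas taken in the hour on nasal cannula would pass for deterioration. Section 5.1 links intubation to worsening while on NIV, and both arms follow the same 4:1 cycle, so this would not by itself favour either arm. It lends no support here.

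**Conclusion.** The point holds. The primary event is an open-label decision on criteria that set no threshold, so the stated sameness is one of headings only. Following the plan as written leaves the primary comparison open to arm-dependent thresholds in either direction.

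The documents do not show that such a difference will occur, nor which way it would run, and its size cannot be derived from them. The error rates above are conditional on 30 per arm, two-sided 0.05 and the assumed gaps. On those terms, a net difference of three patients in 30 is enough to matter. That the duty physician decides is not itself the defect; the defect is that the decision is not anchored to anything measurable.

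**What to change.** Before enrolment:

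1. The trial's clinicians set a closed list of measurable intubation criteria, including cut-offs and the reference measurement, to apply in both arms. The values are theirs to choose. The bedside decision stays with the duty physician.
2. At each intubation, record which criterion was met and the values at that time.
3. Log patients who meet a criterion but are not intubated.
4. Pre-specify, in the protocol or the analysis plan, a supporting analysis by allocated arm of criterion met or intubated, and report intubations outside the criteria by arm.

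The cost is a wording change and one extra case-report-form page, largely using values already collected. Some intubations will be recorded as outside the criteria. No additional patients are needed. The reason for a decision is hard to recover reliably later, so the record has to be in place from the first patient.

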### Data management

5.2

The responsibilities of the designated study team include project compliance, data collection, abstraction and entry, data reporting, regulatory monitoring, problem resolution and prioritization, and coordination of the activities of the protocol study team.

The collected data for this study will be transferred to a secure database managed by the HMC IT team (e.g., PACS). All data generated in this study will be the property of HMC.

Source documentation will be available to support the computerized patient record. Study personnel will record clinical data in each patient's source documents (i.e., the patient's medical record). The study team will maintain adequate and accurate records to enable the conduct of the study to be fully documented and the study data to be subsequently verified. After study closure, the investigators will maintain all source documents, study-related documents, and the data stored in the database used for data collection. Data will be entered throughout the trial as patients are enrolled.

### Statistical methods

5.3

Data analysis will be carried out by the principal investigator with the help of a biostatistician. Descriptive statistics will be used to summarize and determine the sample characteristics and distribution of parameters related to demographic, presenting signs and symptoms, laboratory findings. The normally distributed data and results will be reported with mean and standard deviation with corresponding 95% confidence interval.

## Methods: monitoring

6

### Data monitoring & auditing

6.1

The clinical trial master file will be kept along with informed consent from the patients according to the Joint Commission International, Medical Research Center (MRC), and the Ministry of Public Health (MoPH) requirements.

Any side effects or adverse events related to the trial will be reported to the hospital research committee and MRC.

A regular registration report will be generated to monitor patient accrual and completeness of registration data. A routine data quality report will be generated to assess missing data and inconsistencies. Accrual rate and extent and accuracy of evaluations and follow-up will be monitored periodically throughout the study period, and potential problems will be brought to the attention of the study team for discussion and action. Random-template data quality and protocol compliance audits may be conducted by the study team, at a minimum of once per year or more frequently if indicated. Data safety and monitoring will be conducted according to the HMC-IRB, Ethics, and Data Safety Monitoring Board regulations.

## Ethics and dissemination

7

### Research ethics approval

7.1

The study will be conducted in full conformance with principles of the “Declaration of Helsinki”, Good clinical practice (GCP) and within the laws and regulations of MoPH in Qatar.

### Protocol amendments

7.2

None

### Informed consent

7.3

The researcher will do screening from the patient pool; those patients found to be eligible as per inclusion and exclusion criteria will be interviewed to discuss the trial if accepted, they will be enrolled in the study the PI where the participant will be given free time to decide to participate or not the consenting process will start by screening then interviewing the eligible patient explaining about the trial rationale benefits risks and objectives his or her right to participate or not to participate without being affected and the right to withdraw at any time.

### Confidentiality

7.4

Patients’ data will be coded and kept in a secure database with a unique username and password to maintain patient confidentiality. Only the authorized research team will be granted access to the patients’ electronic charts and reports.

### Access to data

7.6

Data collected in this study will be transferred to a secure database managed by the HMC IT team (e.g., PACS). All data generated in this study will be the property of HMC.

### Dissemination policy

7.7

The findings of this trial will be published as jointly co-authored manuscripts in international medical journals subject to peer review and deposited into the US National Library of Medicine made freely available to the public.

## Abbreviations

Abbreviations: ARDS = acute respiratory distress syndrome, COVID- 19 = coronavirus disease, ICU = intensive care unit, NIV = non-invasive ventilation, PEEP = positive end expiratory pressure.
